### Outcomes

2.4

Primary outcomes are EEG electrocortical activity, i.e., spatial (RO1) and temporal (RO2) changes in different frequency bands. Outcomes will be compared between FOG and normal unimpaired walking, and between cued vs. non-cued walking (RO3) (cf. Statistical methods) to determine the effectiveness of the cueing intervention.

Secondary outcomes are fNIRS spatial (RO1) and temporal (RO2) FOG-related changes in hemodynamic activity, i.e., changes in oxygenated and deoxygenated hemoglobin, as well as changes in percentage time frozen and a pre-specified set of spatiotemporal gait parameters (step length, cadence, gait speed, and gait asymmetry and variability) together with ground reaction force measures. Outcomes will be compared between FOG and normal unimpaired walking, and between cued vs. non-cued walking (RO3) (cf. Statistical methods).

### Participant timeline

2.5

Participants will attend two measurement days at the lab in order to reduce exhaustion and fatigue-related influences. The first lab visit will be used for screening and familiarization. An overview of the study will be provided and all necessary participation documents, such as informed consent, will be checked for completion. Subsequently, screening tests, including the Montreal Cognitive Assessment (MoCA) (Nasreddine et al., 2005), Movement Disorder Society Unified Parkinson’s Disease Rating Scale (MDS UPDRS) Part 3 (Goetz et al., 2008), Freiburg Visual Acuity test (Bach, 1996), and test of vibration sensitivity using a 128 Hz vibration fork (for further information cf. Screenings) will be administered. Head circumference will be measured to ensure proper fitting of the EEG-fNIRS cap. Body measurements will be taken in preparation for the motion capture at the second lab visit. These measurements include height, weight, leg length, knee width, ankle width, shoulder offset, elbow width, wrist width and hand thickness for each side of the body (Plug-in Gait Reference Guide - Nexus 2.12 Documentation, Vicon Documentation, VICON; Oxford, United Kingdom) (Vicon, 2023). Four reflective markers will be attached to the participants hip that are required to run the treadmill in self-paced mode. Participants will then put on a safety harness and commence a 15-minute familiarization period with the treadmill’s self-pace mode. Throughout this phase, participants will be instructed to adjust their walking speed to familiarize themselves with the self-paced feature within the virtual environment. Day 1 will proceed with regular medication. After screening and familiarization, participants will be provided with questionnaires through a digital platform (cf. Screenings). Once the participant has completed the questionnaire, the experimenter will verify that all questions have been answered without reviewing the content of the responses at this stage. All screening procedures and the familiarization on the treadmill will be performed and supervised by trained sport and exercise scientists with experiences in the field of movement science, motor control and neuroscience.

On the second day, the session will start with participants being prepared for motion capture by applying reflective markers to the whole body and putting on a safety harness, followed by a short re-familiarization with the treadmill’s self-paced mode. Once comfortable, preparations for neurophysiological measurements will proceed. Participants will be seated and a cap, already equipped with 64 EEG electrodes, will be aligned on their head using anatomical landmarks (nasion, inion and preauricular points). Electrodes will be prepared with gel, followed by preparation of all optodes until adequate signal quality for both EEG and fNIRS is achieved (cf. sections Electroencephalography (EEG) and Functional near-infrared spectroscopy (fNIRS) for detailed information). The experimental procedure will begin with a detailed instruction of the virtual walking task and testing procedure. Participants are then performing a maximum of four walking trials, each lasting roughly 10 min. Before every trial, participants are asked to stand still for 1 min, which will serve as a baseline period for neurophysiological analyses. After each trial, a short break will be administered. If the total number of FOG episodes is below 15 and the patient is reporting a moderate amount of exertion, the next trial will be initiated. Exertion will be assessed using objective measures, including the Rate of Perceived Exhaustion Scale (Borg, 1982) and the Rating Scale Mental Effort (Zijlstra and Van Doorn, 1985). Participants will perform two blocks, each consisting of four walking trials. A break of 10 to 30 min will be provided between both blocks. Cueing and no-cueing will be administered in alternation. After 15 FOG events, the experiment will be stopped after completion of the current trial. The rationale for this design choice is to collect a sufficient number of FOG episodes, while not over exhausting participants. After the walking task 2, further questionnaires regarding the usability and feasibility of the prototype will be handed to the participants (cf. Screenings). For an overview of the whole procedure, see Figure 1. The neurophysiological preparations and measurements will be undertaken by the same personnel described above, who are trained in the preparation and application of various neuroimaging methods.

**FIGURE 1 F1:**
[figure not shown]
Flow chart of the participant timeline. This figure displays the procedure on both assessment days. MoCA, Montreal Cognitive Assessment; MDS UPDRS III, Part 3 of Movement Disorder Society Unified Parkinson’s Disease Rating Scale; EEG, Electroencephalography; fNIRS, Functional near-infrared spectroscopy. At the end of DAY 2 participants are asked to fill out further questionnaires to gather participant recommendations for the vibrotactile prototype used (cf. Screenings). *Each 10-min walking trial includes a 1-min baseline period immediately before trial onset.

### Sample size

2.6

An *a priori* sample size estimation was conducted using G*Power (v.3.1.9.4) for a linear multiple regression, fixed model with R^2^ increase, assuming an alpha level of 0.05, a power of 0.80, one primary predictor, and a total of five predictors (including covariates). We selected a moderate to large effect size of partial R^2^ = 0.25 (i.e., f^2^ = 0.33), informed in part from findings of Handojoseno et al. (2015b) on EEG electrocortical activity changes associated with transitions to FOG episodes (Handojoseno et al., 2015b). Additionally, as we plan to assess multiple FOG trials per person and condition (up to 15 trials) and analyze them using linear mixed effects models, which typically have higher statistical power than traditional aggregated mean analyses, we anticipate achieving sufficient power to detect effects even if they are somewhat smaller than initially estimated. The selection of 15 FOG episodes is driven by Cockx et al. (2024), who reported a median of 15 FOG episodes per participant and observed significant effects on neurophysiological changes, suggesting that up to 15 FOG episodes per participant may serve as a reasonable benchmark for achieving sufficient statistical power in the analyses (Cockx et al., 2024).

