**Methods:**

Thirty people with Parkinson’s Disease and FOG will be recruited. They will undergo screening and familiarization before performing different walking tests in virtual reality using the Gait Real-time Analysis Interactive Lab (GRAIL). Participants will perform two experimental blocks, each consisting of four walking trials of approximately 10 min. A break of 10 to 30 min will be provided between blocks. Walking with or without vibrotactile cueing will be performed in alternation. During walking, electrocortical (EEG), hemodynamic (fNIRS), kinematic data (3D motion capture), and kinetic data (force plates) will be recorded. Data will be analyzed to investigate spatiotemporal and frequency characteristics of electrocortical and hemodynamic brain activity related to FOG and the impact of vibrotactile cueing on neural signatures and gait improvements in FOG.

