This research is motivated in particular by the limited evidence on the neural aspects of FOG and how effective countermeasures, such as vibrotactile cueing, can contribute to improvements of FOG related gait disturbances in everyday life. We will use a virtual walking scenario with automatic doorways to induce FOG to address three main research objectives. These objectives will focus on the neural mechanisms and pathways underlying FOG (RO1, RO2) and vibrotactile cueing (RO3). Our first research objective (RO1), aims to identify the cortical brain regions involved in FOG that show differential activation prior to the kinematic onset of FOG compared to normal, unimpaired walking. In the literature, the involvement of various brain regions such as frontal and central areas is reported (Asher et al., 2021; Cao et al., 2021; Handojoseno et al., 2015b; Shine et al., 2014). We expect involvement of similar brain regions (cf. perceptual dysfunction hypothesis (Bardakan et al., 2022)) in our virtual doorway scenario, but we also hypothesize differential activation based on the increased realism and environmental complexity achieved through the use of virtual reality. Second (RO2), we aim to delineate the neural signatures of induced FOG episodes, focusing on the temporal and frequency dynamics within the cortical areas of interest. Based on previous research we are expecting to see FOG specific changes in various frequency bands of interest, including alpha, beta and theta up to 5 s prior to FOG onset (Handojoseno et al., 2012, 2015b; Shine et al., 2014). To this end, we will compare FOG episodes vs. unimpaired walking through virtual doorways. Furthermore, we will analyze the connectivity of these dynamics across the brain regions involved. We expect to observe FOG-related changes in coherence, including increased theta coherence in fronto-central regions as reported previously (Shine et al., 2014).

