#### Statistical methods

2.8.4

To address our main research objectives, we will employ linear mixed effects models for our analyses. These models are well-suited for handling repeated measures and allow us to take advantage of the multi-trial data structure, while also accounting for both within-subject and between-subject variability. FOG episodes will be analyzed separately by motor context, distinguishing walking-FOG (forward locomotion, including doorway passage and straight walking) from turning-FOG (360° turning). Each FOG type will be compared against its corresponding unimpaired movement (Handojoseno et al., 2015a). The number of FOG episodes per type and participant will be reported.

First, we will identify cortical brain regions showing differential activation prior to the kinematic onset of FOG. Dependent variables include spatiotemporal characteristics of electrocortical and also hemodynamic brain activity that will be compared between FOG episodes and the corresponding period of unimpaired walking or turning. Second, we aim to delineate the neural signatures of FOG episodes, focusing on the temporal and frequency dynamics within the cortical areas of interest as defined by the first part of our analysis. This step includes analyzing the coherence of the neural dynamics across the brain regions involved. Lastly, we will examine if and how vibrotactile cueing may alter the neural signatures of FOG described above and whether it contributes to improved gait behavior when walking through virtual environments. This analysis will also focus on the reduction of the percentage time frozen, changes in kinematic and kinetic aspects of gait. All analyses will include relevant covariates, such as disease stage, motor symptom severity, prior experience with cueing and random effects accounting for inter-subject variability, and to investigate interindividual differences. To address the large number of comparisons across modalities, all analyses will include appropriate correction for multiple comparisons to control the rate of false-positive findings, using established methods such as Bonferroni correction or cluster-based permutation testing (Maris and Oostenveld, 2007).

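### The stated power of 0.80 is for one uncorrected test at alpha 0.05, but the plan corrects a whole family of primary EEG tests, so 0.80 is not shown for any of them

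*Protocol article*

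**What the plan says.** **Section 2.6 (Sample size)** bases its calculation on a "linear multiple regression, fixed model with R^2^ increase". The error rates and the number of predictors entered are then listed: "assuming an alpha level of 0.05, a power of 0.80, one primary predictor, and a total of five predictors (including covariates"). For the effect it says "We selected a moderate to large effect size of partial R^2^ = 0.25 (i.e., f^2^ = 0.33"). It does not print the resulting N; the planned number is in the abstract ("Thirty people with Parkinson’s Disease and FOG will be recruited"). The section adds that several episodes per person will be analysed with linear mixed models, "which typically have higher statistical power than traditional aggregated mean analyses", and infers that effects a little smaller than assumed would still be detectable.

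**Section 2.4 (Outcomes)**: "Primary outcomes are EEG electrocortical activity, i.e., spatial (RO1) and temporal (RO2) changes in different frequency bands". These are compared between freezing and unimpaired walking, and between cued and non-cued walking. The Introduction names at least three bands ("including alpha, beta and theta up to 5 s prior to FOG onset") and describes the trial as confirmatory.

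**Section 2.8.4 (Statistical methods)** analyses walking-FOG and turning-FOG separately and states that "all analyses will include appropriate correction for multiple comparisons to control the rate of false-positive findings". Bonferroni and cluster-based permutation are given as examples. The number of tests is not fixed.

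**The concern.** The power calculation and the analysis section describe different tests. Section 2.6 has one test at the full 0.05. Sections 2.4 and 2.8.4 have several primary EEG tests, none of them exempt from correction. A corrected test has a stricter threshold and so, for the same N and effect, less power.

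What is at stake is how a null result is read. In a study that calls itself confirmatory, a negative finding on RO1, RO2 or RO3 would be weighed against 80% power, although that figure was never worked out for a test the study will carry out.

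**Working it through.** **Inputs.** From section 2.6: alpha 0.05, power 0.80, one tested predictor, five predictors in total, partial R² = 0.25. From the abstract: N = 30. Assumed: m, the number of tests sharing the 0.05.

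**Effect size.** f² = R²/(1 − R²) = 0.25/0.75 = 0.333, which agrees with the protocol's 0.33.

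**Formula.** For an R²-increase test the statistic is noncentral F with df1 = 1, df2 = N − 5 − 1 = N − 6 and noncentrality λ = f² × N. Power is the probability that it exceeds the central F critical value at the chosen alpha.

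**Step 1: the plan's own figure.**
- N = 26: λ = 8.67, df2 = 20, power 0.7996 (0.7956 with f² = 0.33), just short of 0.80.
- N = 27: λ = 9, df2 = 21, power 0.816 (0.812 with f² = 0.33). The stated inputs therefore require 27.
- N = 30: λ = 10, df2 = 24, power 0.858 (0.855 with f² = 0.33).

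The planned 30 exceeds 27, so the difference is on the safe side. It would follow from 10% dropout (27/0.90 = 30) or from a target power of 0.85, but section 2.6 states neither.

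**Step 2: the same model at a Bonferroni level.** Replace 0.05 by 0.05/m, with f² = 1/3. Power is per test.

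| m | Example of such a family | Alpha per test | Power at N = 30 | N for 0.80 | Smallest partial R² with 0.80 power at N = 30 |
|---|---|---|---|---|---|
| 1 | single test | 0.05 | 0.858 | 27 | 0.22 |
| 2 | two FOG types, one band | 0.025 | 0.774 | 32 | 0.26 |
| 3 | three named bands | 0.0167 | 0.718 | 35 | 0.28 |
| 6 | three bands × two FOG types | 0.0083 | 0.616 | 41 | 0.32 |
| 9 | three bands × three objectives | 0.0056 | 0.554 | 44 | 0.34 |

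The margin of 30 over 27 is used up at the second test. From the third test on, the planned effect of 0.25 is clearly below what 30 participants can detect with 0.80 power.

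**Step 3: can repeated episodes make up the loss?** Let r be the between-person variance of the effect divided by twice the residual episode variance. Averaging m_e episodes per condition, instead of using one, multiplies the variance of a person's contrast by (r + 1/m_e)/(r + 1). For m_e = 15:
- r = 0: (0 + 0.067)/1 = 0.067
- r = 0.25: (0.25 + 0.067)/1.25 = 0.253
- r = 1: (1 + 0.067)/2 = 0.533

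The gain can be large or modest, depending on r. Section 2.6 gives no variance components, and it does not say whether the partial R² of 0.25 refers to a single episode or to a participant's average. If it already refers to averages over a similar number of episodes, the gain is in the figure already. The offset cannot be computed from the document.

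**The case against.** **The planned analysis is not the regression used for sizing.** This stands. The actual analysis is a within-person mixed model on repeated episodes, and its power cannot be derived from section 2.6. A reader might infer that the study certainly lacks 80% power; the document supports only that this power has not been shown. Step 3 indicates that repeated episodes could offset the correction if the effect varies little between people.

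**Mixed models may indeed add power.** This also stands. It is tempting to say that, once by-participant slopes are fitted, they add nothing over a paired comparison of participant means. That is not true in general: episode counts will differ between participants, and a random-slope model weights people by precision. The weakness of the sentence in section 2.6 is that it is unquantified and is used only to cover smaller effects, not multiplicity.

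**Bonferroni need not be used.** Correct. Cluster-based permutation does not divide alpha by the number of channels, so the table does not carry over to it. A reader might multiply 64 electrodes by three bands and quote a very low power, but no such Bonferroni family appears in the plan. Permutation also does not remove the issue by itself: unless bands, FOG types and objectives are tested in one permutation family, correction across them remains.

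**The shortfall is small for two tests.** True: 0.774 against 0.80. The plan also speaks of primary outcomes without requiring all of them to succeed, and the chance of at least one success is higher than the per-test figures.

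**The family and the random effects may be set out in an analysis plan.** Possibly, and their absence here is not the point. The point is that a power figure was published for a test that the same document does not plan.

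**Conclusion.** The point holds as a mismatch between sections 2.4, 2.6 and 2.8.4: the alpha and power in section 2.6 describe no planned primary test. On the protocol's own regression model with f² = 1/3 and N = 30, per-test power falls from 0.86 (one uncorrected test) to 0.77, 0.72, 0.62 and 0.55 with Bonferroni over 2, 3, 6 and 9 tests. These figures rest on an assumed number of tests, on Bonferroni, and on one observation per person.

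Two further inferences are not supported. One is that the analysis would inflate type I error through random intercepts alone: section 2.8.4 promises random effects for inter-subject variability and for interindividual differences, which is compatible with random slopes, and nowhere specifies an intercept-only model. The other is a particular loss from participants who do not freeze on the day: the documents give no such rate, and daily freezing at entry, the 360° turns and testing after 12 h without medication all make freezing more likely.

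**What to change.** No additional enrolment is needed. Choose one of two routes:

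1. **One primary contrast.** Name a single EEG contrast (band, region, time window, FOG type, comparison and cue condition) to be tested at 0.05. On the section 2.6 model, state power 0.86 with 30 evaluable participants, with 0.80 reached at 27. Put all other EEG tests in a corrected second tier. Which contrast to name is for the study team to decide.
2. **A defined family.** Fix the list of primary tests and the correction method, and restate power at the corrected level. Preferably do this by simulating the planned mixed model, with by-participant random slopes for freezing versus unimpaired movement and for cue condition, over a stated range of variance components and episode counts.

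Under either route, delete the sentence claiming sufficient power from mixed models, or replace it with the simulated figure.

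The cost is wording in sections 2.4, 2.6 and 2.8.4, plus a simulation under the second route. The stated power for the corrected tests will be less favourable than 0.80 unless the simulation shows otherwise. The change should be made before any outcome data are analysed.

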### Recruitment

2.7

This study will be conducted at the University of Münster (Germany). The recruitment process will be carried out in cooperation with local Parkinson networks. Participants will be recruited by scientific staff via different channels including homepage advertisement and social media announcements, presentations at local Parkinson’s groups, personal contacts, local sport clubs and other non-profit associations as well as advertisements in local newspapers. Individuals expressing interest will be subject to a standardized telephone interview (10–15 min) to ascertain their eligibility based on predefined inclusion and exclusion criteria (cf. Eligibility Criteria). They will receive detailed information about the procedures of the study and must obtain medical approval before participation. Additionally, they are required to be accompanied by a healthy person when visiting our laboratory. Prior to enrollment, all participants will provide written consent to participate in this study.

### Methods: data collection, management, and analysis

2.8

#### Data collection methods

2.8.1

##### Virtual walking scenarios

2.8.1.1

The virtual walking scenarios are implemented within the Gait Real-time Analysis Interactive Lab (GRAIL) (Motek Medical; the Netherlands). The GRAIL system integrates a 3D instrumented split-belt treadmill with two embedded force plates and a running surface of 1 m (width) x 2 m (length). Lateral handrails are attached to the treadmill, and two non-visible laser barriers are positioned at the front and rear ends for participant safety. Additionally, participants will be equipped with a safety harness connected to a ceiling load cable to mitigate the risk of falls. A stop button is in place on the experimenters’ control desk to promptly halt the treadmill in emergency situations. The GRAIL system also incorporates a marker-based, passive optical motion detection system (Vicon Motion Systems Ltd; Oxford, United Kingdom) (see Kinematics and Kinetics for further details) The virtual scenario is projected onto a semi-cylindrical 180° projection screen (2.4 m x 5 m) using three serially-connected RGB projectors. Another serially connected RGB projector projects onto the treadmill. To ensure accurate detection of visual stimulus presentations on the projection screen, a photodiode is fixed to the bottom center of the projection screen, imperceptible to participants. The photodiode detects any change in light intensity and therefore is used to detect an auxiliary projection (i.e., a white dot) that is synchronized with task-related stimuli displayed on the projection screen (Maas et al., 2024).

The treadmill is synchronized with the virtual environment and will operate in self-paced mode. The participants are able to walk at their preferred walking speed on the treadmill through the virtual environment. Participants are able to control their walking speed individually via their physical position on the treadmill using four reference markers on their hip. The reference point is placed 10 cm in front of the center of the treadmill. The front boundary is 55 cm in front of the center (45 cm from the reference point) and the rear boundary is 40 cm behind the center (50 cm from the reference point). Forward movements, i.e., moving the position of the markers in front of the reference point, accelerates the treadmill. Walking near the reference point maintains the current speed. When the markers are behind the reference point, the treadmill decelerates.

Virtual scenarios will be created with D-Flow (Motekforce Link, Amsterdam, the Netherlands). The virtual scenarios depict a hospital-like environment (see Figure 2) with an endless corridor with wooden flooring (brownish color) and a city scenario in a pedestrian zone. In the hospital scenario, which will be described here as an example, participants walk through a hospital-like corridor that contains visual representations of doors to other rooms (patient bedroom, dinner, medical specialists) to the right and left of the corridor in a well-lit environment. In addition, the scenario includes other smaller decorative objects (e.g., flower pots, benches, poster boards, lighting and ventilation, or trolleys) and occasional intersections with further decorative enrichments. These details aim at providing a more realistic and immersive virtual environment. The main aspect of the virtual hospital scenario are opaque automatic doorways. These doorways are used to mimic typical narrow doorways/passages in the real world that often cause FOG in PD (Cockx et al., 2023). The doors are designed as sliding doors with a motion sensor placed directly above the door. Behind some doors, objects such as a bench, potted flower, or trolley moving laterally toward the participant are presented randomly to introduce unpredictable events during the scenario. The automatic doors open bidirectionally at a speed of 0.3 m/s. They begin to open when the participant is positioned between 3.1–4 m (pseudorandomized, in steps of 0.1 m) in front of them. The doors open to a width ranging from 74 and 100 cm (pseudorandomized, in steps of 1 cm). The scenario contains 10 doors, each separated by approximately 30 m. A rotation symbol is projected onto the floor 8.5 m behind each door. The symbol consisted of two arrows pointing in the same direction and forming a circle, indicating that participants had to perform a 360° rotation. Once participants reached the floor-projected rotation cue and came to a stop, an enlarged version of the same cue was additionally displayed in the center of the screen. The required turn direction followed a fixed alternating sequence across the ten doors, always starting with a right turn at the first door, resulting in five right turns and five left turns.

